### Ethics and dissemination

2.11

The study will be carried out following national and international norms (declaration of Helsinki) related to ethical aspects. This study protocol (version 1, November 15, 2016) was approved by the Ethical Committee of Clinical Investigation of the *Institut Universitari d’Investigació en Atenció Primària (IDIAP) Jordi Gol*, on March 15, 2017 (code P17/091). In addition, the study has been authorized by the Direcció Assistencial d’Atenció Primària of the ICS. The data included in the SIDIAP database will be anonymized and will be identified by an internal code, making subject identification impossible even by the investigative team, thereby guaranteeing the confidentiality of the data of the study participants included in the study according to the organic law on the protection of personal data (15/1999 of 13 December, LOPD). As the study is based on the analysis of an anonymized database, informed consent will not be collected from the patients. Any alteration of the study protocol will be submitted to the ethical committee of the IDIAP Jordi Gol for approval and will be published in clinical trials.gov.

The results of the study will be disseminated through informative meetings addressed to professionals of the ICS, communications to congresses, publications in scientific journals, and in the clinical trials.gov webpage.

### Safety

2.12

The CDS-NVAF may influence clinical decision-making and may contribute in improving the adequacy of anticoagulant treatment in patients treated with VKAs. Changes in treatments are expected (from VKAs to DOACs), which would induce a decrease in the incidence rates of thromboembolic and hemorrhagic events in the medium and long term. Nonetheless, the monitoring of possible adverse effects will be carried out by the comparison of the incidence rates of the studied events between the 2 groups (intervention and control), monthly during the period of the intervention. If an increase in the incidence rates in the intervention group is detected at anytime, the CDS-NVAF will be deactivated by the principal investigator of the project. A data monitoring committee will not be established, as the evaluation of the adverse effects will be carried out by the SISAP in coordination with the principal investigator of the project.

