**Methods and analysis::**

Randomized clinical trial in 287 PCCs, formed by 2 groups (intervention and control). Population: patients controlled in PCCs, diagnosed with NVAF 1 year before the implementation of the decision support tool and with VKA treatment over a minimum of 1 year. A simple randomization method will be performed at a sector level. The decision support tool will be available for 1 year. The time in therapeutic range (TTR) will be available in the digital clinical history only to professionals of the intervention group. The information system for primary care research development database will be used for the data extraction. Statistical analysis will be done at 3 time points: before the implementation of the tool, at 1 year, and at 2 years after the beginning of the intervention. Multilevel (patient and professional levels) logistic regression models will be used to estimate the effect of the intervention.

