### Sample size

2.4

In a first approach the information system for primary care research development (SIDIAP) established that during 2015 PCCs of the ICS had registered 171,472 cases of NVAF, 73,632 of whom were receiving anticoagulant treatment (63,001 VKAs and 10,631 DOACs). Assuming a weight of 90%, an alpha error of 5%, a control versus intervention ratio of 1, corrected for the design by clusters and assuming a loss of 10%, our study will be able to detect a difference of 1% for a rate of thromboembolic events of 0.66%. Despite this power, a clinically relevant relative reduction of 10% will be established.

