### Masking

2.6

The study will be blind for the trial participants, investigators of the project and data managers, but will not be blind to the physicians.

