#### Primary outcomes

2.8.1

(1)Incidence rate of thromboembolic events (acute myocardial infarction or angina, ischemic stroke, peripheral embolism, or transient ischemic attack [TIA]).(2)Incidence rates: Hemorrhagic events (intracranial hemorrhage, gastrointestinal hemorrhage); All-cause mortality.(3)Adequacy of anticoagulant treatment: This variable encompasses the adequacy of the anticoagulant treatment, taking into account if an adequate change has occurred or not. The adequacy of the AT in patients with NVAF will be based on the fulfillment of the criteria of the ministry of health, social services and equality of Spain, 2016^[11]^ (Table 2).

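### The safety rule switches the tool off on any monthly excess in the intervention group, so a tool with no effect would probably be deactivated by chance; sections 2.6 and 2.12 also need reconciling on who is blind

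*Protocol article*

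**What the plan says.** Section 2.12 (Safety) provides for "comparison of the incidence rates of the studied events between the 2 groups (intervention and control), monthly during the period of the intervention". The consequence is fixed: "If an increase in the incidence rates in the intervention group is detected at anytime, the CDS-NVAF will be deactivated by the principal investigator". There is no data monitoring committee. SISAP evaluates adverse effects in coordination with the principal investigator.

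The abstract sets the length of exposure: "The decision support tool will be available for 1 year". Section 2.8.1 (Primary outcomes) lists the events that the monitoring would naturally cover: "Incidence rate of thromboembolic events (acute myocardial infarction or angina, ischemic stroke, peripheral embolism, or transient ischemic attack [TIA", and "Hemorrhagic events (intracranial hemorrhage, gastrointestinal hemorrhage); All-cause mortality".

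Section 2.5 (Randomization) allocates 15 sectors. Section 2.6 (Masking) states: "The study will be blind for the trial participants, investigators of the project and data managers"; only physicians are unblinded.

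**The concern.** The trigger is an increase of any size and the action is mandatory. When two groups share the same true rate, one of them has the higher observed count in almost every month, and it is the intervention group about half the time. Repeating that comparison monthly over several event types makes a chance excess very likely.

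The planned year of exposure is at stake. If the rule is followed, the tool may be withdrawn within months for no real reason, and the randomised comparison at 1 and 2 years would then describe a much weaker intervention. If staff quietly disregard chance excesses, the operating safety rule becomes unwritten discretion.

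A second, smaller matter is that acting on a between-group excess sits badly with the statement that project investigators are blind.

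**Working it through.** The plan states no false-alarm probability for this rule, so there is no figure of its own to reproduce.

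**Inputs from the protocol article**
- Anticoagulated patients 73,632, loss 10%, ratio 1 (section 2.4): 73,632 × 0.9 / 2 ≈ 33,134 per arm.
- Thromboembolic rate 0.66% (section 2.4).
- Target benefit: 10% relative reduction (section 2.4).
- Looks: 12, from 1 year of monthly comparisons (abstract and section 2.12).

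**Assumptions**
- 0.66% is annual.
- The arms are equal in size.
- The three outcomes are independent.
- Haemorrhage is 0.5% and death 3% a year.
- In the three-outcome runs, any benefit applies equally to all outcomes.

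**Step 1. One month, thromboembolic events.** Expected events per arm are 33,134 × 0.0066 / 12 = 18.2. For two Poisson counts with this mean, P(intervention > control) = 0.467. With a true 10% reduction it is 0.346.

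**Step 2. Single-month reading, 12 looks, thromboembolic events alone.**
- No effect: 1 − (1 − 0.467)^12 = 0.9995.
- 10% reduction: 1 − (1 − 0.346)^12 = 0.994.

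**Step 3. Cumulative reading.** Ignoring ties, the chance that a symmetric random walk is never positive over 12 steps is C(24,12)/2^24 = 0.161.
- One outcome: 1 − 0.161 = 0.839.
- Three independent outcomes: 1 − 0.161^3 = 0.996.

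Poisson simulation, which allows for ties, gives slightly lower values:

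| True effect | Thromboembolic only, cumulative | Three outcomes, cumulative | Thromboembolic only, single months |
|---|---|---|---|
| None | 82–83% | 99.5% | 99.9% |
| 10% reduction | 58–59% | 90% | 99.4% |
| 20% reduction | 35% | 64% | 96% |

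**Step 4. First look.** With no effect, the one-month probabilities of an excess are 0.467, 0.462 and 0.484 for the three outcomes. The rule fires at month 1 with probability 1 − 0.533 × 0.538 × 0.516 = 0.85.

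**Step 5. Sensitivity.** With half of 63,001 (VKA patients only) per arm and all three outcomes at 0.66%, the cumulative no-effect figures are 83% and 99.4%. With a 10% reduction they are 59% and 93%. An assumed between-sector coefficient of variation of 0.1 to 0.2 moves the no-effect figures to 78–81% and 99.0–99.3%. None of this rescues the rule.

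**Step 6. If detection meant a test.** An unadjusted one-sided 2.5% test on cumulative data at each look fires with no effect in about 10–11% (one outcome) or 28% (three outcomes). With sector variation of 0.1 to 0.2 and three outcomes at 0.66%, this becomes 33–43%.

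**Masking, side by side.** Section 2.6 says that project investigators and data managers are blind. Section 2.12 has SISAP evaluate between-group rates in coordination with the principal investigator, who must deactivate the tool when the intervention group is higher. That role therefore learns at least the direction of the comparison when a trigger occurs. The text does not say how much more is shared.

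**The case against.** **The article condenses a fuller protocol.** A threshold may stand there, and the word for detection may imply a test. Section 2.10 does set a 5% level, but nothing links it to the monitoring. Section 2.12 states a trigger and a mandatory action, so adding a threshold elsewhere would change the rule rather than fill a gap. Step 6 shows that an unadjusted test would still leave a substantial false-alarm rate.

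**Caution is a legitimate choice.** It is. But a rule that fires at the first look in about 85% of trials with no effect on three outcomes hardly separates harm from chance.

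Three stronger readings are tempting, and the documents do not support them:
- *Even a beneficial tool would almost surely be switched off.* This holds for single-month comparisons at the 10% target. On cumulative data the chance is 58 to 90% at a 10% reduction and 35 to 64% at 20%. Section 2.12 does not say which data are compared.
- *The 1- and 2-year effects could not be estimated.* Deactivation ends exposure, not follow-up. Outcomes still come from SIDIAP, and the as-randomised comparison remains available, though diluted.
- *The principal investigator sees by-group rates and masking is lost in the first month.* Section 2.12 does not say so; coordination is compatible with SISAP passing on only a decision. The consequence is also limited, because outcomes are coded events from an anonymised database.

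**Conclusion.** The concern holds. As written, the rule would deactivate a tool with no effect in about 83% of trials (thromboembolic events alone, cumulative) to about 99% (three outcomes, cumulative), and in essentially all trials if single months are compared. At the protocol's own 10% target it would still fire in about 58% to 90% on cumulative data and over 99% on single months. The likely result is exposure cut short by chance and diluted comparisons.

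The exact percentages rest on the assumptions listed above. The haemorrhage and death rates in particular are not in the documents. The conclusion with no effect does not depend on them, since the closed forms in steps 2 and 3 are close to what any event rate gives unless events are very few.

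On masking, the conclusion is only that sections 2.6 and 2.12 conflict as worded and must be reconciled.

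**What to change.** In section 2.12, replace the any-increase trigger with a pre-specified statistical monitoring boundary on cumulative events. State which event types it covers, compute it with sector-level variance, and have the trial team calibrate it over all looks and event types for two properties: its false-alarm rate and its chance of detecting a real excess.

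Both properties matter, so a conventional threshold should not be borrowed unchecked. For illustration, a cut-off of z = 3.09 that ignores clustering gives 5–17% false triggers on three outcomes with an assumed sector coefficient of variation of 0.1 to 0.2. Even so, it detects a true 20% thromboembolic excess in only about 19% of trials. No particular value is recommended here.

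Reconcile section 2.6 with section 2.12. One way is for SISAP to hold the by-group results and send the principal investigator only a continue or deactivate message.

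The cost is rewording two sections and a calibration exercise, using the structure already in place. The downside should be stated openly: modest true excesses would be acted on later, or not at all during the intervention.

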## Discussion

3

This is the first study to provide family physicians in primary care in Catalunya with a clinical decision support tool (CDS-NVAF) to improve the adequacy of anticoagulant treatment in patients with NVAF. The implementation of CDS-NVAF and its posterior evaluation is currently considered to be a strategy of priority by the ICS to improve the management of patients with NVAF and subsequently reduce thromboembolic and hemorrhagic complications and death derived from poor control of VKA anticoagulation.

The present study may have a positive immediate impact on clinical decision-making at the primary care level, with CDS-NVAD influencing the daily clinical practice of the general practitioners in ICS. On confirming the good results expected, the use of the CDS-NVAF can be extended to all ICS patients diagnosed with NVAF in Catalunya.

The study has received financial support to evaluate the results of 2 years after the beginning of the intervention, however, taking into account the importance of obtaining more knowledge on the impact of healthcare results in the mid or long term, the investigative team is seeking financial support to assess the impact of CDS-NVAF at 5 years postintervention.

The results obtained in the study may be of interest to all of Spain as well as other countries with similar healthcare models which use support tools for clinical decision-making.

With regard to the limitations of the study, the SIDIAP database includes secondary data, and thus, there may be a certain level of underregistration of variables of interest, although this should not differ between the 2 study groups. The quality of the registry is guaranteed in that most of the study variables make up part of different indicators of quality (SHCQ and SQPP) which are incentivated in the payment systems for objectives of the ICS. There is no problem in the registry of the treatment variables as the billing system of the pharmacy offices collects these data. Another limitation is that the study is unblinded for physicians and there may be contamination between groups which may limit the conclusions of the study. Nonetheless, we aim to evaluate the effectiveness of the intervention in the real-life setting related to the usual clinical practice in which this type of situation is frequent. The investigative team believes that randomization by sectors and not by physicians will reduce the probability of contamination between groups. Another limitation of the study is that the tool provides information about the adequacy of the VKA but not the adequacy of the DOACs, which should be taken into account in result interpretation.
